**Primary outcome: cardiometabolic health**			
	**Cardiometabolic risk**		
		Stressor-level heart rate variability	Everyday Discrimination Scale SOC^a^ task
	**Cardiometabolic health behaviors**		
		Sleep quality	Pittsburg Sleep Quality Index
		Diet	Food Behavior Checklist
		Overall health	36-Item Short Form Health Survey
		Subjective assessment of overall health	Self-Developed Scale
		Impairment due to overall health	Self-Developed Scale
		Exercise	International Physical Activity Questionnaire–Short Form
**Secondary outcomes**			
	**CSPs’^b^ threat to leaving the workforce (psychological well-being)**		
		Psychological well-being	Brief Symptom Inventory
		Emotion	Self-Assessment Manikin
		Closeness to community	Inclusion of Other in the Self Scale–Community Version
		Trauma history	Traumatic Life Events Questionnaire
		Burnout	The COVID-19 Burnout Scale Maslach Burnout Inventory
		Job satisfaction	Job Satisfaction Survey
		Psychological agency	Coder-rated measures based on SOC
		Reflective functioning	Coder-rated measures based on SOC
	**Intervention acceptability**		
		Savoring uptake	Self-developed questionnaires
		Intervention acceptability	Self-developed questionnaires
	**Community reach**		
		Number of days CSPs worked	Information obtained from agency
		Number of health-related events offered	Information obtained from agency
		Retention of community members in programs	Information obtained from agency
		Community attendance at events	Information obtained from agency

^a^SOC: stream-of-consciousness.

^b^CSP: community service provider.

#### Secondary Outcomes

Secondary outcomes include threats to CSPs leaving the workforce, which will be assessed via psychological well-being (ie, agency, burnout, and job satisfaction) and intervention acceptability. For these secondary outcomes, we will use the Brief Symptom Inventory-18 [46], the Self-Assessment Manikin [47], the Inclusion of Other in the Self Scale–Community Version (IOS-C) [48], the COVID-19 Burnout Scale [49], the Maslach Burnout Inventory [50], the Traumatic Life Events Questionnaire [51], and the Job Satisfaction Survey [52]. RS intervention acceptability and savoring uptake will be assessed via self-developed questionnaires. All these will be assessed before the intervention, after the intervention, and at the 3-month follow-up.

Finally, the CSPs’ delivery of cardiometabolic health programming to the community will be measured in an exploratory manner. This will be assessed via the number of days the CSPs worked, the number of health-related events offered, the retention of community members in the programs offered by the CSPs, and the number of community members attending the events. Data from the time following the introduction of RS will be compared with those from the 6 months preceding the introduction of RS. This information will be obtained from the health agencies’ institutional data. It is worth mentioning that these measures are not a reflection of the CSPs’ effectiveness, given that the CSPs may meet with fewer community members at any given time yet effectively support them in improving their health outcomes. Likewise, given different structures or job tasks across agencies (eg, leading groups, doing outreach, and follow-ups), there might be differences in how these measures are analyzed in the future. The collection of these data will not enable us to detect differences between the intervention and waitlist control groups. We intend to collect these data on the CSP’s delivery of health programming to lay the groundwork for a more in-depth future investigation of the impact of RS.

The measures and tasks used to assess the secondary outcomes are described in the following sentences:

Brief Symptom Inventory: the participants will report on their psychological well-being using the Spanish version of the Brief Symptom Inventory-18 [46], an 18-item measure assessing depression (eg, During the past week including today, how much were you distressed by feelings of worthlessness?), anxiety (eg, During the past week including today, how much were you distressed by nervousness or shakiness inside?), and somatization. Items are rated on a 5-point scale ranging from 0 (not at all) to 4 (extremely). Previous studies have demonstrated good reliability and validity in HL samples [53].Self-Assessment Manikin: the participants will report on their emotions using the Self-Assessment Manikin [47], a widely recognized nonverbal pictorial measure that assesses emotional states, valence, and arousal levels using pictures to represent how a participant is feeling in response to stimuli.IOS-C: the participants will report on closeness to the community using IOS-C [48]. This single-item pictorial measure uses Venn‐like diagrams—each diagram represents different degrees of overlap of 2 circles, progressing through 7 equal steps, representing lower and higher levels of closeness as the circles overlap more and more. The Inclusion of Other in the Self Scale has good test-retest reliability and convergent validity and has been used in samples with a large percentage of HL participants [54].Traumatic Life Events Questionnaire: the participants will report their trauma history using the Spanish version of the Traumatic Life Events Questionnaire [51], a 23-item scale measuring whether an individual has experienced a wide range of traumatic events, including sexual assault, exposure to combat, or the unexpected death of a loved one, on a scale ranging from 0 (never) to 4 (≥5). Previous studies have demonstrated good reliability and validity in HL samples [55].The COVID-19 Burnout Scale: the participants will report on their COVID-19 related burnout using the COVID-19 Burnout Scale [49], a 10-item scale that measures burnout feelings related to the pandemic. Items (eg, When you think about COVID-19 overall, how often do you feel hopeless?) are scored on a scale ranging from 0 (never) to 6 (all the time).Maslach Burnout Inventory: the participants will report on their occupational burnout using a Spanish version of the Maslach Burnout Inventory [50], a 22-item scale that measures occupational exhaustion, depersonalization, and level of personal accomplishment related to work. Items (eg, I have become more callous to people since I have started doing this job) are scored on a scale ranging from 0 (never) to 6 (every day). Previous studies have demonstrated good reliability and validity in HL samples [56].Job Satisfaction Survey: the participants will report on their job satisfaction using the Spanish version of the Job Satisfaction Survey [52], a 36-item assessment measuring attitudes related to the job and aspects of the job. Items (eg, I feel I am being paid a fair amount for the work I do) are scored on a scale ranging from 1 (disagree very much) to 6 (agree very much). Previous studies have demonstrated good reliability and validity in HL samples [57].Savoring uptake: after completing the intervention, the participants will reflect on the savoring experience using the savoring uptake questionnaire that was developed for this study. The 6-item questionnaire measures the frequency at which participants have engaged in savoring since their last session, how useful they found savoring, how valuable they found savoring, whether they would recommend the program to others, and whether they would like to continue savoring on their own time. Items are scored on a scale ranging from 1 (not at all likely, useful, or valuable) to 5 (extremely likely, useful, or valuable).Intervention acceptability: the participants will report on the acceptability of the RS intervention by completing the Relational Savoring Acceptability Questionnaire, a 14-item assessment created for this study to capture how participants feel before they begin the program (eg, I expect the program will improve my feelings about my work) and how they feel after they complete the program (eg, The program improved my health and well-being) on a scale ranging from 1 (strongly disagree) to 5 (strongly agree).

### Intervention

Consistent with prior work, the RS intervention will involve 4 weekly sessions, each lasting approximately 30 minutes, consisting of 2 phases: memory selection and memory reflection (Textbox 1).

Relational savoring: intervention phases.
**Phases and steps**
Memory selectionRecall a few memories of positive connectedness or attachment content when helping community members.Participants describe these memories and interveners ask follow-up questions designed to reveal the level of specificity, positivity, connectedness, and potential for spoiling in the memories.Interveners select one specific memory with the best content for the next phase.Memory reflection (5-step guided reflection)Sensory reflection (eg, Where were you? What did your surroundings look like? What could you hear?)Emotion reflection (eg, What did you feel?)Meaning making (eg, What did you think?)Future-oriented reflection (eg, What do you think will happen in the future thanks to this connection?)Mind-wandering reflection (eg, What else comes to mind?)

RS is a manualized intervention that has been adapted to allow CSPs the opportunity to savor memories of providing care to community members to enhance their sense of connectedness to the community [24,28]. In this study, as in previous studies, the intervention will be delivered by paraprofessionals (eg, undergraduate and postbaccalaureate students) [28]. Previous studies have shown that the intervention can be administered with high fidelity by paraprofessionals with a low level of clinical training (4 h of didactic training plus approximately 4 h of practice-based training) [28].

At the beginning of RS, the CSPs will complete a 1-minute mindfulness exercise, which is consistent with prior studies [28,29]. Next, during the first phase of the RS intervention (*memory selection*), the CSPs will be guided to generate memories of the times when they felt closeness, connection, or joy when they were able to support, encourage, or protect community members. The participant will be guided to select a memory with substantial attachment content (ie, secure base and safe haven memories). Alternatively, if the participant is unable to produce a memory explicitly related to safe haven or secure base content, they may select a memory involving a moment of positive connectedness or togetherness [28]. Then, during the second phase (*memory reflection*), the CSPs will engage in a 5-step guided process, where they will reflect on sensations, emotions, and cognitions associated with the selected moment. Sessions will be conducted via Zoom (Zoom Video Communications, Inc) by trained bilingual and bicultural research assistants in the participant’s language of choice (Spanish or English). The RS sessions will be recorded and transcribed to assess themes that emerge during the savoring sessions and to analyze therapist fidelity and therapist-client relationship quality. In addition, immediately before and after each intervention session, the participant will complete a 2-question survey assessing the participant’s mood (Self-Assessment Manikin) and perceived closeness to the community (IOS-C) [47,48].

### Data Analytic Plan

Descriptive statistics will be used to analyze the demographic characteristics of our sample population. A series of analyses of covariance will be conducted to examine the effects of RS on HRV, health behavior, psychological well-being, threats to CSPs leaving the workforce, and the reach of CSPs’ cardiometabolic health programming. We will compare outcomes at baseline, immediately postintervention, and at the 3-month follow-up across participants in the experimental versus waitlist group. HRV at baseline will be included as a covariate in analyses examining HRV, and all analyses will examine a range of potentially confounding covariates for potential use in analyses (eg, age, BMI, and socioeconomic status; those that are significantly associated with key study variables will be included as covariates in hypothesis testing). Effect sizes will be examined in all analyses. With a sample size of 80, it will be possible to detect small-to-moderate effects (yielding an effect size *d*=0.24) of RS on the CSPs’ cardiometabolic health, threats of CSPs leaving the workforce, and the delivery of cardiometabolic health programming. As stated in the *Eligibility Criteria and Recruitment* section, our goal is not to detect statistically significant effects but rather to look for effect sizes to inform future studies.

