**Methods:**

We will recruit a sample of 80 CSPs from community health agencies serving low-income HL populations. Participating CSPs will be randomized into an experimental or a waitlist control. Participants will complete 1 or 2 baseline assessment batteries (before the intervention), depending on the assigned group, and then complete 2 more assessment batteries following the 4-week RS intervention (after the intervention and at a 3-mo follow-up). The RS intervention consists of guided reflections on positive moments of connection with others. Electrocardiogram data will be obtained from a wearable device (Polar Verity Sense or Movisens) to measure heart rate variability. The primary outcome is cardiometabolic health, consisting of cardiometabolic risk (obtained from heart rate variability) and cardiometabolic health behaviors. The secondary outcomes include CSPs’ threats to leaving the workforce (assessed via psychological well-being), intervention acceptability, and CSPs’ delivery of cardiometabolic health programming to the community (exploratory). Analyses of covariance will be used to examine the effects of RS on cardiometabolic health and on CSPs’ threats to leaving the workforce, comparing outcomes at baseline, postintervention, and at follow-up across participants in the experimental versus waitlist group.

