### Randomization and Overview

In this randomized controlled waitlist design (ClinicalTrial.gov identifier NCT05560893), the CSPs will be randomly assigned to an experimental group or a waitlist group. Both groups will complete an identical assessment battery (assessing health behaviors and psychological well-being) and complete stressor tasks (assessing cardiometabolic risk) before the intervention, after the intervention, and at a 3-month follow-up. The experimental group will receive the RS intervention (4 sessions, 1/wk) 1 week after the baseline assessment (Figure 1). The waitlist group will complete the baseline assessment, wait 4 weeks, complete a second baseline assessment, and 1 week later receive the RS intervention. After completing the RS intervention, the participants in both the experimental and waitlist groups will complete the postintervention assessment 1 week later and a follow-up 3 months later.

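### The stated between-arm comparisons at postintervention and 3 months set treated against treated; the waitlist arm's untreated second baseline is not named as the comparator

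*Protocol article*

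**What the plan says.** The abstract describes the design thus: "Participating CSPs will be randomized into an experimental or a waitlist control". Under Objectives, the hypotheses are framed as RS against the waitlist control condition.

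Randomization and Overview gives the schedule:

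- Experimental arm: "The experimental group will receive the RS intervention (4 sessions, 1/wk) 1 week after the baseline assessment".
- Waitlist arm: "The waitlist group will complete the baseline assessment, wait 4 weeks, complete a second baseline assessment, and 1 week later receive the RS intervention".
- Both arms, once RS is complete: "the participants in both the experimental and waitlist groups will complete the postintervention assessment 1 week later and a follow-up 3 months later".

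The Data Analytic Plan proposes analyses of covariance and says: "We will compare outcomes at baseline, immediately postintervention, and at the 3-month follow-up across participants in the experimental versus waitlist group". The abstract repeats this: "comparing outcomes at baseline, postintervention, and at follow-up across participants in the experimental versus waitlist group". Neither statement mentions the second baseline. The abstract notes only that it exists: "Participants will complete 1 or 2 baseline assessment batteries (before the intervention), depending on the assigned group". For HRV, the plan adds the baseline value as a covariate without saying which of the waitlist arm's two baselines is meant.

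**The concern.** In a waitlist design, the control information comes from the period in which the waitlist arm is still untreated. Here that period ends before the waitlist arm starts RS, and its only outcome measurement after the wait is the second baseline. The visits named for the between-arm comparison fall outside that period: at postintervention and at follow-up, the waitlist arm has had the same four sessions as the experimental arm.

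The stated analysis therefore does not estimate the contrast in the hypotheses. It estimates how early RS differs from RS given a few weeks later. The plan says that its aim is effect sizes on which later studies can be planned. A between-arm estimate centred near zero, whatever the benefit of RS, would misinform that planning.

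**Working it through.** **1. The plan's own figure.** The article gives no figure for this contrast. Its only effect-size figure is d=0.24 for 80 participants, with no power or sidedness stated. With 40 per arm (1:1 assumed) and a two-sided 5% test, the smallest effect detectable with 80% power is (1.96 + 0.84) × √(2/40) = 2.80 × 0.2236 ≈ 0.63, so 0.24 is not reproduced. Nothing below depends on it.

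**2. The timeline**, rebuilt from Randomization and Overview:

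| | Experimental | Waitlist |
|---|---|---|
| First baseline | week 0 | week 0 |
| Second baseline (untreated) | none | week 4 |
| RS, 4 weekly sessions | weeks 1–4 | weeks 5–8 |
| Postintervention | about week 5 (2nd battery) | about week 9 (3rd battery) |
| 3-month follow-up | about weeks 17–18 (3rd battery) | about weeks 21–22 (4th battery) |

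At each visit labelled postintervention or follow-up, both arms have had four sessions and are equally far past them. The arms differ only in calendar time, delay to treatment and number of earlier assessments.

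**3. The algebra.** Write μ for the untreated mean, δE and δW for the RS effect in the experimental and waitlist arms, and aE and aW for any order, delay or calendar effect.

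- Stated contrast: (μ + δE + aE) − (μ + δW + aW) = (δE − δW) + (aE − aW). With δE = δW and aE = aW this is 0, however large the RS effect.
- Experimental postintervention (about week 5) against waitlist second baseline (week 4): (μ + δE) − μ = δE. This neglects any drift over the one-week gap. Both are second batteries, so repeat testing is balanced.

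**4. Numerical check.** Simulated ANCOVA with the first baseline as covariate, 40 per arm, SD 1, complete data and the same RS effect in both arms once treated. The allocation and the correlation between visits are assumptions, not figures from the article.

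| True d | Visit correlation | Stated contrast, mean estimate (post; follow-up) | Experimental post vs waitlist second baseline: mean estimate (power) |
|---|---|---|---|
| 0.24 | 0.5 | −0.002; 0.002 | 0.24 (23%) |
| 0.5 | 0.5 | −0.001; 0.00 | 0.50 (71%) |
| 0.5 | 0.6 | 0.00; 0.00 | 0.50 (77–78%) |
| 0.8 | 0.5 | 0.001; 0.00 | 0.80 (98%) |

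The stated contrast rejects in about 5% of runs throughout, which is the nominal error rate. As a rough check on the power at d=0.5, the standard error is √(1 − r²) × √(2/40). That is 0.194 at r=0.5 and 0.179 at r=0.6.

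**5. What a non-zero result would mean.** With an assumed order effect of 0.1 SD in the waitlist arm and a true RS effect of 0.5, the stated contrast averages −0.10 at both visits. It returns the assumed artefact and nothing of the RS effect. The size 0.1 is only illustrative; the article gives no basis for any value.

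**The case against.** The strongest reply is that the article's sentence is a summary and that the authors intend a calendar-matched comparison, in which the experimental postintervention visit is set against the waitlist second baseline. The hypotheses name the waitlist control condition. Only the waitlist arm has a second baseline, paid separately at US $40 (Ethical Considerations), and that battery has little purpose except as the untreated comparator. The timeline figure is not visible, and an analysis plan that is not shown may say more. On this reading the postintervention contrast is valid.

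Part of this stands: the design does contain a sound control measurement, and it cannot be said that the investigators will not use it. But the visit labels are defined in the text for both arms: "After completing the RS intervention, the participants in both the experimental and waitlist groups will complete the postintervention assessment 1 week later". The analysis section uses those labels and does not name the second baseline. This is a positive statement that conflicts with the schedule, not a detail left to another document. The calendar-matched reading also cannot rescue the 3-month comparison, because the waitlist arm has no untreated data after week 4.

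A second reply is that this is a pilot that disclaims significance testing. That makes power secondary, but it makes bias in the effect size the central issue.

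Three stronger inferences are tempting, and the article does not support them:

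- *That the problem affects every outcome.* Community reach is compared with the 6 months before RS was introduced, and the Secondary Outcomes section concedes that those data cannot separate the arms. Savoring uptake and post-programme acceptability have no untreated counterpart.
- *That the trial must show nothing.* Zero is expected only under the conditions above, and within-person change would remain visible, though uncontrolled. What is lost is the randomised estimate.
- *That the second-baseline data are already in hand.* The article reports 79 enrolled by November 2023 and collection expected to continue until May 2024, and gives no count of second baselines. They are scheduled; no more can be said.

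**Conclusion.** The concern holds for HRV, the health behaviours and the psychological well-being, burnout and job-satisfaction outcomes. Read with the article's own visit definitions, the between-arm comparison at postintervention and at 3 months is treated against treated, and does not test the stated hypotheses. Its expected value is zero if RS works equally in both arms and there is no order, delay or calendar effect. Otherwise it reflects a different response to delayed RS, the extra assessment or the shift in time, not RS against no RS.

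The zero is algebra and needs no assumed correlation. The power figures do depend on the assumed allocation, complete data and correlation of 0.5 to 0.6; the Limitations section expects missing ECG data, so for HRV they are optimistic. The defect lies in the stated analysis, not in the randomised design, and should be corrected before the between-arm results are analysed. For the 3-month visit no wording can supply a randomised comparison with untreated participants.

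**What to change.** In the abstract's Methods and in the Data Analytic Plan:

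1. Define the randomised contrast as experimental postintervention versus waitlist second baseline, by ANCOVA adjusted for the first baseline. State that the HRV baseline covariate is the first baseline in both arms.
2. Present the waitlist arm's own pre-post change and all 3-month data as uncontrolled within-person estimates, with no between-arm efficacy claim.
3. Report the actual elapsed time from first baseline at the two visits in the randomised contrast, since the schedule implies about 5 weeks against 4. With 79 of 80 participants enrolled by November 2023, reporting is the practical remedy; rescheduling would change little.
4. Leave community reach, savoring uptake and post-programme acceptability outside this contrast.

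The cost is wording, plus giving up a randomised 3-month claim that the design cannot support. No new visit is needed, because the second-baseline battery is already in the schedule and in the payment plan.

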### Measures

#### Primary Outcomes

All the constructs and measures assessed are summarized in Table 1.

All assessments are available in both English and Spanish. Cardiometabolic health, as indicated by cardiometabolic risk and cardiometabolic health behaviors, will be the primary outcome and will be measured before the intervention, after the intervention, and at the 3-month follow-up. Cardiometabolic risk will be measured via HRV in response to a stressor task. The stressor task will consist of a discrimination stream-of-consciousness (SOC) task [35,36], where participants will talk for 4 minutes about an occasion where they felt discriminated against. Before completing the SOC task, participants will complete a questionnaire [36] that will provide them with a list of commonly occurring discrimination events from which they can select an event that has occurred to them. Vagally mediated HRV will be calculated from the variability of the interbeat intervals obtained from electrocardiogram (ECG) data. ECG data will be recorded using a Polar Verity Sense heart rate monitor or Movisens device, small wearable devices that the participants will place in their arm or chest, respectively, during the stressor task and at rest (before and after the stressor task baseline measures). Favorable cardiometabolic health behaviors include behaviors pertaining to sleep, exercise, and diet and will be assessed using the Pittsburgh Sleep Quality Index [37], the International Physical Activity Questionnaire–Short Form [38], the Food Behavior Checklist [39], the 36-Item Short Form Health Survey [40], and 2 self-developed scales (subjective assessment of overall health and impairment owing to overall health).

The measures and tasks used to assess the primary outcome, cardiometabolic health, are described in the following sentences:

1. Everyday Discrimination Scale: the participants will complete a Spanish version of the Everyday Discrimination Scale [36], a 9-item scale that assesses the frequency and the attribution of discrimination experiences (eg, In your day-to-day life, how often are you treated with less respect than other people are?) to assist them in identifying a discrimination experience to speak about in the SOC task. Items are rated on a scale of 0 (never) to 5 (almost every day), with higher scores indicating a higher frequency of discrimination experience. Previous studies have demonstrated good reliability and validity in HL samples [41].

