2. SOC task: after a 2-minute baseline task (sitting with no stimuli), the participants will be asked to select an experience of discrimination to focus on for a SOC task. To help them do this, the participants will complete a brief questionnaire of common discrimination experiences, followed by a 5-minute interview to help them select among the experiences reported on the questionnaire. This cardiovascular reactivity task is modeled after a SOC task previously used in our laboratory [35], modified to be ecologically relevant to this population. The SOC task will ask the participants to speak for 4 minutes about the discrimination experience, focusing on the thoughts and feelings they had. The participants will then complete a 2-minute resting-recovery task wherein they will speak about a positive memory. The prompt for the SOC task is as follows (prompt translated to Spanish and available in English and Spanish, based on participant’s preference):

For the next four minutes, I would like for you to please discuss in detail your experience during this time that you have identified when you felt [insert discrimination experience here]. Please discuss your thoughts, feelings, hopes, and concerns about the experience. Remember, there are no right or wrong answers, so please say whatever comes to mind. Your job is to talk continuously about anything that comes to mind about this experience for the 4-minute period. We will record your responses because how you are thinking and feeling about this experience is very important to us.

3. Pittsburgh Sleep Quality Index: the participants will report on their sleep quality using the Spanish version of the Pittsburgh Sleep Quality Index [42], a 10-item measure that assesses sleep quality and duration. Items (eg, How many hours of actual sleep do you get at night—this may be different than the number of hours you spend in bed?) are rated on a scale of 0 to 3, whereby higher scores reflect more sleep disruption. Previous studies have demonstrated good reliability and validity in HL samples [43].

4. Food Behavior Checklist: the participants will report on their diet using the Food Behavior Checklist for Spanish speakers [39], a 16-item questionnaire that measures basic dietary behaviors, including the frequency of fruit, vegetables, juice, and low-fat dairy consumption; food insecurity; shopping; and cooking techniques. Previous studies have demonstrated good reliability and validity in HL samples [44].

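### Baseline is listed as a visit at which the arms are compared and is also the HRV covariate; it cannot inform on RS and belongs in the model only as a covariate

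*Protocol article*

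**What the plan says.** The method is given as a set of ANCOVAs: "A series of analyses of covariance will be conducted to examine the effects of RS on HRV" and on the other outcomes. The points of comparison follow: "We will compare outcomes at baseline, immediately postintervention, and at the 3-month follow-up across participants in the experimental versus waitlist group". The Methods paragraph of the Abstract repeats this: "comparing outcomes at baseline, postintervention, and at follow-up across participants in the experimental versus waitlist group".

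The next sentence of the Data Analytic Plan fixes one covariate: "HRV at baseline will be included as a covariate in analyses examining HRV". No baseline covariate is fixed for any other outcome. Further covariates are to be kept only if they prove significantly associated with key study variables.

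The word baseline has more than one possible meaning:

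- **Visit 1**, which both arms attend before any RS.
- **A second visit in the waitlist arm only** (Randomization and Overview): "The waitlist group will complete the baseline assessment, wait 4 weeks, complete a second baseline assessment, and 1 week later receive the RS intervention".
- **A resting recording within each session** (Primary Outcomes). The stressor task comes "after a 2-minute baseline task (sitting with no stimuli"), while the outcome is defined by the stressor: "Cardiometabolic risk will be measured via HRV in response to a stressor task".

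On the later visits, Randomization and Overview states that after completing RS "the participants in both the experimental and waitlist groups will complete the postintervention assessment 1 week later and a follow-up 3 months later".

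**The concern.** A visit that precedes all treatment is listed on the outcome side, alongside the two visits meant to show the effect. Under randomisation the expected arm difference at visit 1 is zero, so including it adds nothing about RS. For HRV the baseline value appears to stand on both sides of the model.

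This matters because the article says that the pilot's product is effect sizes for planning a later trial, not significance tests. A baseline contrast reported as one of those effect sizes is uninformative. A baseline visit absorbed into a single arm effect would shrink the figure passed on to the next trial.

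**Working it through.** **Inputs.** From the article: N = 80, d = 0.24 given as detectable, three comparison visits, and a baseline covariate fixed for HRV only. Assumed: 1:1 allocation (40 per arm), two-sided 5% tests, and between-visit correlation r of 0.4 to 0.8.

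**1. The plan's own figure.** The standard error of d is √(2/40) = 0.2236. The detectable d at 80% power is (1.960 + 0.842) × 0.2236 = 0.626. At d = 0.24 the power is Φ(0.24/0.2236 − 1.960) = 18.8%. The stated 0.24 is therefore not reproduced on these assumptions. That is a separate matter; 0.24 serves here only as a yardstick.

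**2. HRV at baseline.** Let Y₀ be visit 1 stressor HRV. Regressing Y₀ on arm and Y₀ gives a coefficient of 1 on Y₀, 0 on arm, and no residual. In 4,000 simulated trials the largest absolute arm coefficient was about 7 × 10⁻¹⁶, which is rounding error. If the covariate is instead the resting recording, the model is not degenerate, and the arm coefficient shows only chance imbalance.

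**3. Other outcomes at baseline.** The expected arm difference is 0 with standard error 0.2236. The chance of |d| ≥ 0.24 is 2 × [1 − Φ(1.073)] = 0.283. Any null comparison at this sample size has that chance. It shows how easily a baseline contrast could look like a signal.

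**4. If one arm effect were averaged over the three visits.** With later-visit differences d₁ and d₂, the expected value is (0 + d₁ + d₂)/3, against (d₁ + d₂)/2 without baseline. The ratio is 2/3 for any d₁ and d₂ that do not sum to zero. Simulated at r = 0.6 with the visit 1 covariate:

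- differences (0, 0.24, 0.24): 0.161 over three visits, 0.241 over the later two
- differences (0, 0.24, 0.12): 0.121 over three visits, 0.181 over the later two

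If 0.16 were taken forward in place of 0.24, the later trial would need 614 rather than 273 per arm for 80% power, a factor of (3/2)² = 2.25.

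**5. The test under that averaging.** Write the three-visit mean as (Y₀ + 2M)/3, where M is the mean of the two later visits. Adjusting for Y₀ removes the Y₀ term, so the arm coefficient and the residuals are both 2/3 of those for M, and t is unchanged. The simulated t statistics agreed to within 10⁻¹⁴. What shrinks is the difference in raw units, or in units of a fixed SD. An effect size computed from t itself would not shrink.

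**6. The schedule.** Both arms have had RS by their postintervention and follow-up visits. With the same RS effect of 0.24 in both arms, the simulated arm difference was −0.001 with baseline included and −0.001 without it. The two-thirds ratio therefore says nothing about how large the later-visit difference is.

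**7. What the covariate gains elsewhere.** Adjusting a later visit for its visit 1 value multiplies the standard error by √(1 − r²): 0.92 at r = 0.4, 0.80 at r = 0.6 and 0.60 at r = 0.8.

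**The case against.** The best defence is that a series of ANCOVAs reads naturally as one model per visit, or as an arm-by-visit analysis. Neither dilutes anything, and the choice of model is commonly left to a fuller document. Listing baseline might then be no more than a look at balance. This stands against any claim that the plan averages over visits. It does not remove the wording itself: two places name baseline as a point of arm comparison, on a par with the later visits, and no reading makes that comparison informative about RS.

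A reader might also infer several stronger points, which the documents do not support:

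- **That the trial's effect is understated by a third.** Averaging is neither stated nor excluded, so the loss is conditional. A figure such as 0.33 in place of 0.50 SD also presumes an untreated control at the later visits, which the schedule does not provide.
- **That the baseline comparison is void for every outcome.** Self-regression can affect HRV only, and only if the covariate is the same stressor measure.
- **That much power is lost.** At r = 0.6, with a difference of 0.50 SD and 40 per arm, power is 0.91 for the later visits with the covariate and 0.41 for three visits without it. But that contrast changes two things. Later visits without the covariate have standard error √(0.8 × 2/40) = 0.20, z = 2.5 and power of about 0.70, so some 0.21 of the 0.50 drop comes from losing the covariate. With the same-measure covariate kept, no power is lost.
- **That deleting baseline repairs the comparison.** It does not, because the two remaining visits follow RS in both arms.

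**Conclusion.** The point holds as a modest fault in the stated analysis. Baseline should be a covariate and a descriptive row, not a point of arm comparison. For HRV the baseline contrast is exactly zero if the covariate is visit 1 stressor HRV. For other outcomes it describes chance imbalance only. The reduction to two thirds applies if, and only if, one arm effect is averaged over the three visits. It then affects the size of the estimate and, with the same-measure covariate, not the test.

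The ratio of two thirds needs no assumption about correlation or allocation. The 28% figure assumes 40 per arm, and the precision gains rest on assumed correlations. The larger question of which visits contrast RS with no RS remains open after this correction.

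**What to change.** In the Data Analytic Plan and the Abstract:

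- Remove baseline from the list of arm comparisons, and show baseline values by arm descriptively.
- Use the visit 1 value in both arms as the covariate for every outcome measured at visit 1, not for HRV alone. A mixed model with one common baseline mean for both arms would serve equally: baseline then enters as a response, but no baseline arm effect is estimated.
- Say whether the HRV covariate is stressor HRV or the resting recording.
- Estimate arm differences only at post-randomisation visits. Treat the waitlist second baseline as a post-randomisation outcome visit, and not as that arm's baseline covariate.
- Reconcile Randomization and Overview with the Data Analytic Plan on the fact that both arms have received RS by the postintervention and follow-up visits. The edits above do not do this by themselves.

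The cost is a few sentences. No new data or visits are needed.
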